## Abstract

**Background:**

Emergence delirium is a behavioral disturbance after general anesthesia in children and may distress both the patients and the primary caregivers, such as parents and medical staff, looking after the patients. Various medical and emotional interventions have been investigated to reduce emergence delirium; however, none are completely effective. This trial intends to assess whether the mother’s recorded voice can reduce this adverse post-anesthesia event and facilitate arousal from general anesthesia.

**Methods/design:**

This is a prospective, double-blind, single-center, parallel-arm, superiority, randomized controlled trial to be conducted in participants aged 2–8 years who are undergoing elective surgery requiring general anesthesia. Participants will be randomly assigned to one of two groups: those who are stimulated to wake up by listening to their mother’s recorded voice (maternal group, *n* = 33) or a stranger’s voice (stranger group, *n* = 33) during anesthetic emergence. The primary outcome is the initial emergence delirium score in the post-anesthesia care unit (PACU). The secondary outcomes are hemodynamic parameters, including heart rate and mean blood pressure, the duration of time between the cessation of anesthetics and a BIS level of 60, 70 and 80, eye-opening or purposeful movement time, extubation time, total consumption of analgesics, PACU stay time, emergence delirium and pain scores during the PACU stay.

**Discussion:**

This is the first randomized controlled trial to investigate the effect of a mother’s recorded voice during emergence on the pediatric emergence profile after general anesthesia. It may provide prophylactic treatment options to decrease emergence delirium and enhance arousal from general anesthesia.

**Trial registration:**

ClicnicalTrials.gov, ID: NCT02955680. Registered on 2 November 2016.

**Electronic supplementary material:**

The online version of this article (doi:10.1186/s13063-017-2164-4) contains supplementary material, which is available to authorized users.

## Background

Emergence delirium (ED) is described as a “mental disturbance during recovery from general anesthesia consisting of hallucinations, delusions and confusion manifested by moaning, restlessness, involuntary physical activity, and thrashing about in bed” [1]. It can cause self-injury, dressing disruptions, surgical dehiscence, and dislodged indwelling catheters and can lead to parents’ and surgeons’ dissatisfaction with the anesthetic. The incidence of ED in pediatric patients after general anesthesia is reported to be between 10 and 80% [2]. Several factors, such as sevoflurane or desflurane anesthesia, younger age, pain, anxiety and the temperament of the child have been suggested to contribute to ED, but the precise etiology remains uncertain [2, 3]. Various studies have tried to reduce emergence delirium after anesthesia [4–6], but none have been completely effective.

Mothers usually spend a large amount of time with their children. Therefore, mothers can be assumed to contribute to their children’s emotional status and neurological development. In a previous study, maternal voice had special importance and enhanced involuntary attention [7]. Moreover, a mother’s voice elicited stronger activations in specific cerebral regions than an unknown voice in another study [8]. A recorded mother’s voice increased the activation of the prefrontal cortex compared to a stranger’s voice [9]. As shown by these studies, a mother’s voice has been shown to have a strong impact on both behavioral and neuronal responses in children.

However, the influence of a familiar voice, especially a mother’s voice, on a child during anesthetic emergence has been scarcely explored previously. Therefore, we will investigate whether maternal voice supports emotional stability and facilitates emergence during the emergence period. We hypothesized that children would show reduced ED and faster emergence when they heard their mothers’ recorded voices compared to a stranger’s recorded voice.

## Methods

### Study design

This prospective, single-center, parallel-arm, double-blind, randomized controlled trial was approved by the Institutional Review Board (IRB) of Daegu Catholic University Medical Center (CR-16-139-L) and registered at ClinicalTrials.gov (NCT02955680) before enrollment. This trial is conducted in a tertiary university hospital (Daegu Catholic University Medical Center) in South Korea. We report the protocol of this trial according to the SPIRIT guidelines and the SPIRIT flow chart (Fig. 1 and Additional file 1, respectively). This protocol also follows the CONSORT Statement.

**Fig. 1 Fig1:**
[figure not shown]
The SPIRIT flow diagram: the schedule of enrollment, interventions and assessments. *including mean blood pressure and heart rate, *T*
_*1*_ at preoperative waiting area, *T*
_*2*_ cessation of anesthetics, *T*
_*3*_ extubation, *T*
_*4*_ PACU arrival, *T*
_*5*_ 10 min after post-anesthesia care unit (PACU) arrival, *T*
_*6*_ 20 min after PACU arrival, *T*
_*7*_ 30 min after PACU arrival, *T*
_*8*_ PACU discharge, *mYPAS* modified Yale Preoperative Anxiety Scale, *BIS* Bispectral Index, *ET*
_*sevo*_ end-tidal sevoflurane concentration, *PAED* Pediatric Assessment of Emergence Delirium, *FLACC* face, legs, activity, cry and consolability

### Participants

Pediatric patients aged 2–8 years with an American Society of Anesthesiologists physical status (ASA PS) of 1 or 2 who are scheduled to undergo ophthalmology or otorhinolaryngology surgery requiring general anesthesia will be enrolled. Potential participants who meet the inclusion criteria will be recruited at outpatient clinics or during preoperative visits before surgery. The exclusion criteria are described as follows:ASA PS 3 or 4Presence of developmental delays or neurological diseasesDeafness or hearing impairmentsHistory of allergies or contraindications to the use of ketamine (increased intracranial pressure, open-globe injury, or a psychiatric or seizure disorder)Maternal mutismAbsence of the mother

### Ethics, consent and permissions

We will obtain written informed consents from all of the legal guardians of the participants via a single investigator ([name]) prior to any study-related procedures.

### Randomization and blinding

After recruitment, the participants will be randomized to the maternal group or the stranger group with a 1:1 ratio (Fig. 2) using a computerized online tool (www. Randomization.com). A random sequence will be managed and kept within sealed, opaque envelopes by an assistant who is not involved in this study. When a patient is enrolled in the study, an anesthesia nurse will open a sealed envelope and prepare the mother’s or a stranger’s recorded voice file using a voice recorder according to the group allocation. The voice recorder will be delivered to the operating room after the patient arrives and will be connected to noise-cancelling headphones before surgical draping.

**Fig. 2 Fig2:**
[figure not shown]
CONSORT flow chart

Allocations will be concealed to all investigators and participants except the anesthesia nurse who delivers the voice recorder to the investigator. If serious adverse events that threaten the safety of patients occur (such as death or irreversible injury), we will stop the intervention immediately, break the blinding, and contact the IRB.

### Withdrawal, dropout, and discontinuation

Participants are free to withdraw at any time during the trial at their own or their legal representative’s request. If the continuation of the trial may threaten the participant’s health, a participant can be withdrawn based on the investigators’ judgment. Reasons for withdrawal will be recorded in case report form. All data will be analyzed according to the intention-to-treat principle.

### Confidentiality

Personal information including names, social security numbers or chart numbers will not be collected. Only the study code will be collected and managed separately. The collected data will remain confidential until the investigators analyze the data. The final dataset will be managed by the chief investigator (EK). After the completion of the study, the collected data will be encrypted and stored for 3 years and then discarded.

### Intervention

At the preoperative waiting room, patients are premedicated with atropine (0.02 mg/kg) and ketamine (1 mg/kg) administered intravenously in the parental presence. After a patient enters the operating room, standard monitoring (electrocardiography, noninvasive arterial blood pressure, and pulse oximetry) and the Bispectral Index (BIS; VISTATM monitoring system; Aspect Medical Systems Inc., Norwood, MA, USA) will be applied. Anesthesia will be induced using fentanyl (1 mcg/kg) and 5–6% of sevoflurane via a scented facial mask. Rocuronium 0.6–0.8 mg/kg will be given to facilitate intubation. Anesthesia will be maintained with 1.5–2.0 MAC of sevoflurane and 50% oxygen, with a BIS target range of 40–60. At the end of the operation, pyridostigmine and glycopyrrolate will be administered to antagonize neuromuscular blockade. All patients will be given prophylactic antiemetics with dexamethasone 0.1 mg/kg and ondansetron 0.1 mg/kg.

According to the pre-assigned allocation, the patients will be stimulated to wake up by a repeated recording of the mother’s voice (maternal group) or a stranger’s voice (stranger group) at the end of the operation. The voice recording will be performed before the operation. In a calm environment, the mother or a woman who does not know the child is asked to speak the following sentences in her usual tone of voice:“OO (first name of child), wake up. Let’s go home with mommy. OO, wake up. Open your eyes. Take a deep breath.”

Only light patting on the shoulder and the recorded voice will be allowed to stimulate the patients. The recorded voice will be delivered to the patient repeatedly via noise cancelling headphones until extubation. An investigator who is blinded to the assigned intervention (EK) will check the BIS value and the end-tidal sevoflurane concentration (ET_sevo_ %) at the end of surgery, the extubation time, the eye opening or purposeful movement time and the time to BIS values of > 60, 70, and 80 during the emergence period. The BIS value will be included if the electromyography score is < 50% and the Signal Quality Index is > 75%. After gentle suctioning of oral secretions from the oropharynx, extubation will be carefully performed when the participants are able to achieve spontaneous breathing and obey verbal commands. Voice stimulation via headphones will be maintained until the patients arrive at the post-anesthesia care unit (PACU).

### Measurements

The primary outcome measurement is the initial PAED score in the PACU. The secondary outcomes are hemodynamic parameters (heart rate, mean blood pressure), the duration of time from the cessation of anesthetics to a BIS score of 60/70 and 80 (BIS > –60/70/80 time), the eye-opening or purposeful movement time, the extubation time, the total consumption of analgesics, PACU stay time, and PAED, Watcha, and FLACC scores in the PACU.

The Modified Yale Preoperative Anxiety Scale (m-YPAS) will be used when the patients arrive at the preoperative waiting room with their parents before premedication [10, 11]. At the end of surgery, all anesthetics will be stopped immediately and the BIS value and the end-tidal sevoflurane concentration (ET_sevo_ %) are recorded. Hemodynamic parameters, including heart rate (HR) and mean blood pressure (MBP), will be checked at five time points; at the time of the cessation of anesthetics (baseline, t_0_), time to reach a BIS value of 60 (t_1_), time of extubation (t_2_), time of PACU arrival (t_3_), and time of PACU discharge (t_4_). BIS > 60, 70, and 80 times, defined as the time intervals from the cessation of anesthetics until the BIS reached values of 60, 70, and 80, respectively, will be measured. Eye-opening or purposeful movement time is defined as the interval from the cessation of anesthetics to-eye opening or purposeful movement of the patient. Extubation time, defined as the interval from the cessation of anesthetics until extubation, will also be measured.

Upon arrival to the PACU, a blinded investigator will measure emergence delirium and pain scores at every 10 min for the first 30 min. Emergence delirium will be measured by two methods, the Pediatric Assessment of Emergence Delirium (PAED) and the Watcha scales. The PAED scale has five categories (eye contact, actions, awareness, restlessness, and consolability) scored from 0 to 4 and summed to obtain a total score with a range of 0–20 [12]. The degree of emergence delirium increased directly with the total scores. The Watcha scale is a four-point scale as follows [13]: 1, calm; 2, crying but can be consoled; 3, crying and cannot be consoled; 4, agitated and thrashing around. A total PAED score > 12 or a Watcha score > 2 at any time is considered post-anesthetic ED. Pain will be measured by Face, Legs, Activity, Cry and Consolability (FLACC) scores ranging from 0 to 15 [14]. In patients with a total PAED score > 12, a Watcha score > 2 or a FLACC score > 4 in the PACU, fentanyl 0.5 mcg/kg will be administered as a rescue medication and repeated if the agitation does not subside. Adverse events, such as postoperative nausea and vomiting, excessive secretions, laryngospasm, or desaturation and the total consumption of analgesics, will also be measured. The patients will be discharged when they are calm and meet a modified Aldrete score ≥ 9 [15], and the duration of the PACU stay will be recorded as the PACU stay time. The subjective satisfaction of the primary care giver such as a parent or the PACU nurse will be measured just before PACU discharge on a five-point scale as follows: 1, very disappointed; 2, disappointed; 3, so-so; 4, satisfactory; 5, very pleased.

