### Statistical analysis

An intention-to-treat analysis will be performed and missing data will be input with the last-observation-carried-forward method. Continuous variables will be presented as the mean and the SD or the median and the interquartile range (IQR) according to the normality assumption using the Kolmogorov-Smirnov test. Categorical variables will be presented as numbers of patients and proportions.

The primary outcome (the initial PAED score) will be compared with an independent *t* test or a Mann-Whitney *U* test. For secondary outcomes, continuous variables will be compared with an independent *t* test or the Mann-Whitney *U* test and categorical variables will be compared with Pearson’s chi-squared test or Fisher’s exact test. All tests are two-sided and *P* < 0.05 is considered statistically significant. A statistician ([name]) who is not involved in the data collection will conduct all statistical analyses with SPSS software (version 21.0; SPSS Inc., IBM, Chicago, IL, USA).

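### Secondary emergence times are compared without adjusting for the anesthetic depth recorded at time zero; the cost is precision and exposure to chance imbalance, not bias

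*Protocol article*

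**What the plan says.** The Background section makes speed of emergence part of the hypothesis: "We hypothesized that children would show reduced ED and faster emergence" with the mother's voice.

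The Measurements section lists the outcomes that serve it, all secondary. The BIS times are "defined as the time intervals from the cessation of anesthetics until the BIS reached values of 60, 70, and 80", and eye-opening or purposeful movement time and extubation time start at the same point. At that point "all anesthetics will be stopped immediately and the BIS value and the end-tidal sevoflurane concentration" are recorded.

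Under Intervention, "Anesthesia will be maintained with 1.5–2.0 MAC of sevoflurane and 50% oxygen, with a BIS target range of 40–60". BIS values count only when the electromyography score is below 50% and the Signal Quality Index is above 75%.

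Under Statistical analysis, "For secondary outcomes, continuous variables will be compared with an independent" t test or a Mann-Whitney U test. No covariate is named, and missing data are handled by last observation carried forward.

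Under Randomization and blinding, "the participants will be randomized to the maternal group or the stranger group with a 1:1 ratio", with no stratification stated, and "Allocations will be concealed to all investigators and participants except the anesthesia nurse".

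**The concern.** Depth at the moment the clock starts is a likely determinant of how long a child takes to wake. The protocol lets children enter the timed interval from a range of depths, measures that depth on two scales, and then names tests that use neither reading. Part of the spread in emergence times that could be explained is left in the error term, and a chance difference in starting depth between the arms passes into the estimated voice effect.

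The BIS 60 time shows this most directly. The upper end of the maintenance target is the threshold itself, so a child at BIS 58 has almost no interval left and a child at 60 may have none. The protocol does not settle that last case: the Intervention section words the threshold as above 60, and the Measurements section as reaching 60.

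The same outcomes have a related gap. A child with no valid reading at BIS 70 or 80 has no time to analyze, and carrying the last observation forward cannot supply one, because a single time-to-threshold has no earlier value.

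At stake is how firmly the trial can speak on the faster-emergence half of its hypothesis.

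**Working it through.** **Inputs from the protocol.** Planned enrollment 33 per arm (Abstract); two-sided alpha 0.05 (Statistical analysis); power 0.8, PAED difference 1.6, SD 2.19, 30 per group before dropout (Sample size).

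**Assumed input.** The correlation r between starting depth and emergence time within an arm is not given. The range used is 0.3, 0.5 and 0.7.

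**1. The plan's own figure.** n = 2(1.96 + 0.842)² × 2.19² / 1.6² = 29.4, so 30 per group, as stated; 30 × 1.10 = 33 per group gives 66. This calculation concerns PAED only. No figure is stated for the emergence times.

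**2. Chance imbalance in starting depth.** In units of its own SD, the difference between arm means has standard deviation √(2/33) = 0.246. The probability that it exceeds 0.25 SD in either direction is 31%, and that it exceeds 0.5 SD is 4.2%. With 30 per arm these become 33% and 5.3%.

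**3. Effect on the unadjusted comparison.** The shift is r × imbalance. An imbalance of 0.5 SD moves the emergence-time difference by 0.15, 0.25 or 0.35 SD at r = 0.3, 0.5 or 0.7.

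**4. Error rates.** 40,000 trials were simulated with no voice effect, 33 per arm, one normally distributed covariate, t test against ANCOVA. Mean bias was about 0.002 SD or less throughout.

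| r | All trials: unadjusted | All trials: adjusted | Imbalance 0.4–0.6 SD: unadjusted | Imbalance 0.4–0.6 SD: adjusted |
|---|---|---|---|---|
| 0.3 | 5.0% | 5.0% | 7.7% | 5.0% |
| 0.5 | 5.2% | 5.2% | 13.5% | 5.3% |
| 0.7 | 4.9% | 4.9% | 18.9% | 4.9% |

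**5. Precision.** Adjustment multiplies the residual SD, and so the interval width, by √(1 − r²). The unadjusted difference detectable with 80% power is (1.96 + 0.842) × 0.246 = 0.69 SD. Power after adjustment at that difference is Φ(0.69 / (0.246√(1 − r²)) − 1.96).

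| r | √(1 − r²) | Interval narrower by | Detectable difference, adjusted | Power at 0.69 SD, adjusted |
|---|---|---|---|---|
| 0.3 | 0.954 | 5% | 0.66 SD | 83.6% |
| 0.5 | 0.866 | 13% | 0.60 SD | 89.9% |
| 0.7 | 0.714 | 29% | 0.49 SD | 97.5% |

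**The case against.** The strongest reply is that nothing here is an error. Allocation is randomized and concealed, and the investigator who takes the readings is blinded. If the readings come before the voice, starting depth can differ between arms only by chance, and a t or Mann-Whitney test already allows for chance. Step 4 confirms this. A reader might infer that the faster-emergence result would be systematically distorted; the documents do not support that. The raised false-positive rates apply only to trials that happen to have a sizeable imbalance.

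The outcomes are secondary, and a separate analysis plan, which is not shown, could add adjusted analyses. That limits the weight of the point. It does not remove it, because the protocol itself names the method for these outcomes. Nor does the protocol say that the two readings will go unused: they can still be tabulated by group, which would reveal an imbalance without correcting for it.

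The gain rests on an assumed correlation that may differ between the five times, and the constrained maintenance range could weaken it. This also stands.

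Adjustment has a hazard of its own. The Intervention section places both the start of the recording and the depth readings at the end of the operation, without fixing their order. If the voice starts first, BIS at cessation may already carry part of its effect, and adjusting for it could remove some of what is being tested. The fix must deal with this.

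**Conclusion.** The point holds as a moderate improvement to the analysis of secondary outcomes. The planned tests are valid but leave out two likely prognostic readings that the trial already collects. At an assumed r of 0.3–0.7, adjustment would narrow confidence intervals by about 5–29% and protect against an imbalance in mean depth, which has a 31% chance of exceeding 0.25 SD. These figures are for a linear model with a baseline covariate; in a Cox model the gain shows mainly as power, not as a narrower interval.

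Two further inferences should be resisted. The precision figures do not mean that 66 children are too few: that number was derived for PAED, and neither it nor the primary analysis is touched. And the near-zero interval concerns BIS 60 only; it is no argument about BIS 70 or 80, eye opening or extubation.

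**What to change.** For the five emergence times, prespecify a model with group, end-tidal sevoflurane at cessation, BIS at cessation and age. Cox regression, or a regression that allows zero times, would serve; a log-time model fails at zero. Report the unadjusted comparison alongside it.

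Add three statements:

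- Both depth readings are taken before the recording starts, so that they are true baseline covariates. If that cannot be assured, adjust for end-tidal sevoflurane and age only.
- Give one rule, applied alike in both arms, for children already at or above BIS 60 at cessation, and word the threshold the same way in the Intervention and Measurements sections.
- Censor a child without a valid BIS reading at the threshold at the last valid BIS reading, in place of last observation carried forward. Censoring at the end of monitoring would treat a threshold that may have been crossed unrecorded as not reached.

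The cost is slightly more analysis work and reliance on a model for secondary outcomes. Both depth readings are already recorded, so no new measurement is needed, but the order of reading and recording has to be fixed in the study procedure.

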### Sample size

The primary outcome is the initial PAED score. In our pilot study, the mean difference of the PAED score between the stranger group and the maternal group was 1.6 with a standard deviation (SD) of 2.19. To attain an alpha value of 0.05 and a test power of 0.8, 30 patients are needed in each group using the following formula [16]. We plan to enroll a total of 66 patients to allow for a 10% dropout rate:$$ n\kern0.5em =\kern0.5em \frac{2{\left({z}_{a/2}+{z}_{\beta}\right)}^2\kern0.5em \cdotp \kern0.5em {\sigma}^2}{{\left({\mu}_c-{\mu}_t\right)}^2} $$

To compensate for the possibility of an over-estimated effect size of the pilot study, we will perform an interim analysis at 50% enrollment. If the sample size has significantly lower power than our expectation, we will recruit more patients. Otherwise, we will continue the study according to our initial sample size calculation.

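### Serial secondary outcomes have only two-sample tests at unadjusted P < 0.05, implying about 19 time-point tests and leaving the heart rate and blood pressure baseline unused (minor)

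*Protocol article*

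**What the plan says.** All references are to the protocol article.

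- **Haemodynamics (Measurements).** "Hemodynamic parameters, including heart rate (HR) and mean blood pressure (MBP), will be checked at five time points". The first reading is taken "at the time of the cessation of anesthetics (baseline, t_0"; the other four are at BIS 60, extubation, PACU arrival and PACU discharge. Both variables are listed as secondary outcomes.
- **Delirium and pain (Measurements).** From PACU arrival, "a blinded investigator will measure emergence delirium and pain scores at every 10 min for the first 30 min". The Figure 1 legend lists arrival, 10, 20 and 30 minutes, so PAED, Watcha and FLACC have up to four values each. The same section defines emergence delirium as PAED above 12 or Watcha above 2 at any time.
- **Primary outcome.** The initial PAED score in the PACU: one value per child and one test.
- **Analysis (Statistical analysis).** Continuous secondary outcomes are to be compared by independent t test or Mann-Whitney test, and categorical ones by chi-squared or Fisher test. "All tests are two-sided and *P* < 0.05 is considered statistically significant".

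The article gives no repeated-measures method, baseline adjustment, per-child summary for heart rate, blood pressure or pain, or ranking of the secondary outcomes.

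**The concern.** A two-sample test takes one value per child. Given four or five values per child and no stated summary, the natural reading is one test at each time point. Two things follow.

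First, there would be many separate chances to declare significance at 0.05, with nothing to say how an isolated significant time point should be read. A modest but consistent difference along a series could also be missed at every single point.

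Second, heart rate and mean blood pressure have a reading that the protocol itself calls baseline, yet no named test uses it. With 30 evaluable children planned per arm, that gives up precision that costs nothing to recover.

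At stake is how the secondary results are interpreted, not the main conclusion of the trial.

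**Working it through.** **1. The plan's own figure.** The Sample size section states: "the mean difference of the PAED score between the stranger group and the maternal group was 1.6 with a standard deviation (SD) of 2.19". With two-sided alpha 0.05 and power 0.8:

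n = 2 × (1.960 + 0.842)² × 2.19² / 1.6² ≈ 29.4, rounded up to 30 per group.

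This matches the stated 30, and 60 × 1.1 = 66 matches the stated total. The calculation concerns one score at one time, so nothing below changes it.

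**2. Count of implied tests** (from Measurements; assumes one test per time point)

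| Series | Values | Tests |
|---|---|---|
| Heart rate | 5, of which t0 is baseline | 4 |
| Mean blood pressure | 5, of which t0 is baseline | 4 |
| PAED | 4, of which the first is the primary | 3 |
| Watcha | 4 | 4 |
| FLACC | 4 | 4 |
| **Serial total** | | **19** |

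If Watcha, a four-point scale, is treated as categorical, the test changes but the count does not. The single-value secondary outcomes add 7: three BIS times, eye-opening or movement time, extubation time, analgesic consumption and PACU stay. The total is then 19 + 7 = 26. Satisfaction and adverse events are measured but are not in the list of secondary outcomes, so they are not counted.

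**3. Chance of at least one false positive if every null hypothesis is true**

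Under independence this is 1 − 0.95^k:

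- k = 19: 1 − 0.95^19 = 0.62, with 19 × 0.05 = 0.95 false positives expected.
- k = 26: 1 − 0.95^26 = 0.74, with 26 × 0.05 = 1.3 expected.

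The tests are not independent, because they come from the same children. The documents give no correlations, so a range was simulated with equally correlated normal test statistics:

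| Assumed correlation | 19 tests | 26 tests |
|---|---|---|
| 0 | 62% | 74% |
| 0.3 | 52% | 62% |
| 0.5 | 41% | 48% |
| 0.7 | 28% | 32% |

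**4. Value of t0 for heart rate and blood pressure.** Adjusting a later reading for t0 multiplies the variance of the group difference by 1 − r², where r is the correlation between the two readings. The documents give no r.

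| Assumed r | Variance remaining | Standard error smaller by |
|---|---|---|
| 0.3 | 91% | 5% |
| 0.5 | 75% | 13% |
| 0.7 | 51% | 29% |

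This applies to 8 of the 19 tests. The PACU scores have no pre-treatment value.

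**5. Is t0 a true baseline?** The Intervention section starts the voice at the end of the operation. The Measurements section stops anaesthetics at the end of surgery, and t0 is that moment. The order of the two is not stated. If the voice began first, t0 could already carry part of the effect, and adjusting for it could remove some of that effect.

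**6. After the change described under the fix.** Heart rate 1, blood pressure 1 and any-time delirium 1 make 3 tests in place of 19. With the 7 single-value outcomes that is 10, for which 1 − 0.95^10 = 0.40 under independence. Fewer tests therefore do not settle multiplicity alone; the status of the secondary results must also be stated.

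**The case against.** The strongest objection is that a journal article need not describe the modelling of secondary outcomes, and a separate analysis plan may do so. Testing point by point is inferred: a two-sample test could equally be run on change from t0 or on a summary per child. The inference must indeed be labelled as such. But the article does more than stay silent. It names the tests and the significance level, and as named they make no use of a reading it calls baseline.

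Three further objections stand and limit the point.

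- An across-time summary already exists for PAED and Watcha: delirium at any time. It gives one yes/no result per child and suits the named categorical tests.
- Each time-point test uses one value per child, so it keeps its nominal 5% level. A reader might infer that ignoring within-child correlation makes these tests invalid; it does not.
- One pooled arm effect is debatable. The haemodynamic readings run from an anaesthetised child to PACU discharge, and later PACU scores may follow rescue medication that earlier scores triggered.

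A reader might also take 26 as the number of serial tests and 74% as the error rate. The serial count is 19; 26 needs seven outcomes measured once, and 74% needs independence. Nor is a baseline being discarded for delirium or pain, since none is recorded.

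**Conclusion.** The point holds as a minor one. The tests named for secondary outcomes do not suit serial data, and they leave the heart rate and blood pressure baseline unused.

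The implied count is about 19 time-point tests. The chance of at least one false positive is about 62% under independence and 28% to 52% for assumed correlations of 0.7 to 0.3. This rests on the reading that each time point is tested separately and on all null hypotheses being true.

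The precision lost by ignoring t0 cannot be sized from the documents. On assumed correlations of 0.3 to 0.7, adjustment would leave 91% to 51% of the variance, for heart rate and blood pressure only and provided that t0 precedes the voice.

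A reader might infer a threat to the main result. The documents do not support that: the primary outcome is one score at one time with one test, so this point touches neither its type I error nor the sample size.

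**What to change.** 1. **Heart rate and mean blood pressure.** Confirm and state that t0 is recorded before the voice starts. Then fit one longitudinal model for each variable, with arm, time (categorical, since the points are events rather than clock times), arm-by-time and the t0 value, and child as a random effect. Report the arm difference at each of the four later points with a 95% confidence interval, plus one overall test. State in advance whether that test is of the average difference or of all four differences jointly.
2. **PAED and Watcha in the PACU.** Use the existing any-time delirium definition as the single across-time comparison. Note that it includes the initial PAED score and so overlaps with the primary outcome.
3. **Individual PACU time points, including FLACC.** Show group estimates with 95% confidence intervals and do not declare significance at each time.
4. **Status.** State that only the initial PAED score is confirmatory.

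The cost is a few sentences of plan wording and slightly more analysis work. No new data are needed. The article reports recruitment as ongoing, so the wording should be settled before the final analysis.
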